**Figure 2 F2:**
[figure not shown]
Participant flow diagram.

#### Blinding

To minimise bias and possible contamination, the coaches in this trial will be employed by Monash University and will be independent of the Developmental Regression clinic. The coaches working with the participants in the Coaching+FF group will not be in contact with participants in the FF group.

The FF programme will be implemented through the Induk (https://induk.io/) technical infrastructure, which securely encodes participant accounts using anonymous unique identifiers for each participant. This mediated approach ensures that potential bias from administrators or the research team is effectively eliminated. Given that this is a pragmatic trial, it is not possible or appropriate to blind parent participants (ie, parents would know if they would access coaching).

The questionnaires for collecting primary outcome data and other parent-reported outcomes are administered and captured by REDCap, thereby maintaining the blinding of researchers to treatment allocation and ensuring consistent data collection.

#### Sample size

This study will enrol eligible families of children seen at Monash Children’s Developmental Regression Clinic who have consented to taking part in this intervention trial.

As there was a lack of available effect size estimates for interventions targeting families of children with regression, we used effect sizes from online interventions that aimed to improve mental health, stress and well-being of parents of children with a disability or chronic medical condition.^20^ To calculate the sample size required for *F-*tests (analysis of covariance (ANCOVA) and analysis of variance (ANOVA)), G*Power 3.1.9.7 software was used.^41^ To detect a large effect (*f*= 0.5) in the primary outcome (ie, parental stress) with a power of 80% and α of 0.05 (two-tailed), a sample size of 43 parents is required. To allow an attrition of approximately 30% between baseline (T0) and follow-up assessment (T2), a sample size of 56 parents (28 per group) is required.

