**Methods and analysis:**

This study is a prospective, pragmatic randomised controlled trial comparing the effectiveness of online parent coaching plus Family Focus (Coaching+FF) to Family Focus alone (FF) for primary carers of children experiencing developmental regression. A sample of 56 families will be randomised in a 1:1 ratio. Outcomes are assessed at baseline, post-intervention and 12-month post-randomisation. The primary outcome is parental stress symptoms at post-intervention. Secondary outcomes include parental depressive and anxiety symptoms, parental engagement in health-promoting activities, family empowerment, family quality of life and child global health outcomes. The study will also examine the uptake and acceptability of specific coaching and FF components and explore the facilitators and barriers to their delivery and implementation.

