### Aim and objectives

This study aims to evaluate the effectiveness and uptake of a blended approach (Coaching+FF) for primary carers (hereon, ‘parents’) of children experiencing developmental regression, compared with the online programme alone (FF). By using an active comparator in this study, we aim to generate clinically relevant and realistic estimates of the effects of blending coaching and the online intervention,^31^ over and above the effects of the online intervention alone. This approach acknowledges the urgent need for support among families managing child regression concerns and provides a practical framework for evaluating new intervention strategies in this context.

In comparison to parents who engage with FF without coaching (‘comparison group’), the objectives are to determine:

The effects of Coaching+FF (‘intervention group’) on the primary outcome of parental stress symptoms.The effects of Coaching+FF (‘intervention group’) on the secondary outcomes of (1) parental anxiety and depressive symptoms, (2) family empowerment, (3) parental engagement in health-promoting activities, (4) family quality of life and (5) child’s global health outcomes.

We will also explore the proportion of parents in the FF group who transition from above to below the clinical thresholds for stress, anxiety and depressive symptoms at post-intervention. In addition, the uptake and acceptability of online parent coaching and the FF programme will be examined by assessing recruitment and retention rates, user engagement metrics, coaching uptake, programme usage data and participant feedback on perceived usefulness and satisfaction at post-intervention.

We hypothesise that, compared with parents in the FF group, parents in the Coaching+FF group will report lower levels of parental stress, anxiety and depressive symptoms, and greater improvements in family empowerment, engagement in health-promoting activities, family quality of life and child’s global health outcomes. These differences are expected to emerge at post-intervention and follow-up. Further, we anticipate that parents would find online coaching and the FF programme satisfactory and acceptable.

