## Methods

### Study design

The study is a parallel, two-armed, superiority randomised controlled trial (RCT) that examined the effectiveness and uptake of online parent coaching combined with FF. The study is registered with the International Standard Randomised Controlled Trial Number registry (ISRCTN25513446). Data will be collected at baseline (pre-randomisation, T0), post-intervention (6-month post-randomisation, T1) and follow-up (12-month post-randomisation, T2).

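### The sample-size paragraph does not match the primary contrast: 43 is not the two-arm figure, and the one-SD effect comes from online interventions, not from the coaching increment under test

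*Protocol article*

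**What the plan says.** All references are to the protocol article.

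- **Effect and size (Sample size):** "To detect a large effect (*f*= 0.5) in the primary outcome" and "with a power of 80% and α of 0.05 (two-tailed), a sample size of 43 parents is required". The calculation is described as G*Power F-tests, "analysis of covariance (ANCOVA) and analysis of variance (ANOVA"). Numerator df, number of groups, covariates and any correlation are not given. The 43 is raised to 56 for about 30% attrition between T0 and T2.
- **Source of the effect (Sample size):** "we used effect sizes from online interventions that aimed to improve mental health, stress and well-being of parents of children with a disability". The same source also covers parents whose child has a long-term illness. The reason given is that no estimates existed for families of children with regression.
- **Design (Study design; Abstract):** a "parallel, two-armed, superiority randomised controlled trial (RCT"). "A sample of 56 families will be randomised in a 1:1 ratio". "The primary outcome is parental stress symptoms at post-intervention".
- **Contrast (Aim and objectives):** the effect of adding coaching, "over and above the effects of the online intervention alone". Under Trial arms, both groups have access to the Family Focus (FF) programme.
- **Analysis (Data analysis):** a 2 (group) by 3 (time) repeated-measures ANOVA for primary and secondary outcomes.
- **Prior evidence (Introduction):** findings from similar studies of guided online programmes are described as contradictory.

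**The concern.** Two things in one paragraph do not fit the trial.

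First, the arm contrast on stress at T1 has 1 df, and 43 is not the number that contrast requires at the stated effect, power and alpha.

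Second, the planning effect belongs to a different comparison. The stated reason for using a proxy, the lack of estimates in families of children with regression, covers the gap in population. It does not cover the gap in contrast: an effect for online interventions as such is not the effect of coaching added to an online programme that both arms receive.

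The words 'large effect' also hide that, on the two-group reading, the trial is planned around a full-SD benefit of coaching over an active comparator. The stake is interpretation. A reader who takes 80% power at face value could read a non-significant result as evidence that coaching adds little, when moderate added benefits had a poor chance of detection.

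**Working it through.** **Method.** Noncentral F, with noncentrality λ = f²N and df2 = N − groups − covariates. Power is the probability that F exceeds its 5% critical value. For two equal arms, f = d/2.

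**Inputs from the article.** f = 0.5, alpha 0.05, power 80%, two arms 1:1, 56 randomised, about 30% attrition.

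**1. Reproducing 43 (f = 0.5)**

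| Setting | N for 80% power |
|---|---|
| 1 df, 2 groups, 0–2 covariates (the two-arm contrast) | 34 (power 0.807 with no covariate; 33 gives 0.795) |
| 2 df, 3 groups, 0–1 covariate | 42 |
| 2 df, 6 groups, no covariate | 42 |
| 2 df, 6 groups, 1 covariate | 43 (power 0.810; 42 gives 0.7996) |
| 2 df, 4 groups, 3 covariates; or 2 groups, 5 covariates | 43 (same df2) |
| Univariate repeated measures, 2 groups, 3 times, correlation 0–0.9: between-group | 13–32 |
| Same, group-by-time interaction | 4–15 |

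So 43 can be reached with 2 numerator df. It is not given by the 1-df arm contrast or by the standard univariate repeated-measures settings.

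**2. Direction of that mismatch.** Analysed N: 43 × 1.30 = 55.9, hence 56; 56 × 0.70 = 39.2, so about 39. For the two-arm test at f = 0.5:
- N = 39: λ = 0.25 × 39 = 9.75, power 86%.
- N = 43: λ = 0.25 × 43 = 10.75, power 89%.
- N = 56: λ = 0.25 × 56 = 14, power 96%.

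At its own assumed effect, the trial has more than the stated 80%.

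**3. What the effect size means.** f = 0.5 gives d = 2 × 0.5 = 1.0, on the two-group reading only.

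**4. Smallest d with 80% power, unadjusted.** 0.92 at 39, 0.88 at 43, 0.76 at 56. The 30% attrition is stated to T2, so the number available at T1 may lie above 39.

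**5. Power at 39 for smaller increments.** The article gives no coaching increment, so these values of d are assumptions. The adjusted column assumes a baseline correlation of 0.5, which replaces d by d/√(1 − 0.25) and takes one covariate df.

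| Assumed d | Unadjusted | Adjusted, r = 0.5 | Evaluable N for 80%, unadjusted |
|---|---|---|---|
| 1.0 | 86% | 94% | 34 |
| 0.8 | 68% | 80% | 52 |
| 0.5 | 33% | 42% | 128 |
| 0.3 | 15% | 18% | 351 |

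With r = 0.7, power at d = 0.5 is still only 57%.

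**The case against.** **Origin of 43.** A reader might infer that 43 came from entering the six arm-by-time cells as six independent groups of parents. The article does not support that as a fact. Six groups with one covariate matches exactly, but so do other 2-df settings. A multivariate repeated-measures interaction test with two groups and three times needs 42, 44 or 45, depending on the noncentrality convention. Two df is also the df of the group-by-time interaction in the planned ANOVA. What stands is that the inputs are unstated and 43 is not the figure for the arm difference at T1.

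**Power at the planned effect.** A reader might infer that the df mismatch leaves the trial short of power. It does the opposite, raising the required number from 34 to 43.

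**Meaning of f.** The value d = 1.0 belongs to the two-group reading. In a six-cell interaction with arm differences of 0, D and D, f = 0.5 would mean D of about 2.1 SD. The two readings should not be merged.

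**Primary test.** The article does not name a 1-df ANCOVA at T1 as the primary test. It plans a repeated-measures ANOVA. The 1-df contrast is used here because the trial has two arms and the primary outcome is set at one time point.

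**Use of a proxy.** The article is open that it borrows effect sizes, and it does not claim that they come from comparable contrasts. The Introduction notes that 22 of 30 studies in a review of parent interventions combined online content with professional contact. That does not make their effects estimates of what coaching adds, and no comparators or effects are given.

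**Interpretation.** The article does not say that a null result would be read as no effect. The Discussion speaks of preliminary data and warns of limited power. That warning is tied to insufficient sample size, so it does not tell the reader that full recruitment still leaves moderate increments poorly covered.

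**Conclusion.** The point holds in two parts of unequal weight.

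The number 43 does not correspond to the two-arm contrast, which needs 34. This is a reporting fault in the conservative direction and causes no shortfall at f = 0.5.

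The effect size is the material fault. The stated power is tied to a one-SD difference drawn from online interventions as such, while the trial tests only the coaching increment, for which the article offers no supporting figure and describes the related evidence as contradictory. With 39 analysed, the detectable difference is about 0.9 SD unadjusted, and power for an assumed d of 0.5 is 33% (42% with a baseline correlation of 0.5, 57% with 0.7).

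The result of 34 and the power at d = 1.0 rest only on the article's inputs and a two-group, 1-df F-test. The other power figures rest on assumed increments and correlations and on 30% loss by the analysis time point.

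**What to change.** Rewrite the sample-size paragraph:

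1. Restate the calculation for the two-arm contrast on parental stress at T1, naming the test, numerator df, number of groups and covariates.
2. State f = 0.5 as d = 1.0.
3. Say that the source effect sizes are for online interventions and not for the increment from coaching over the online programme alone.
4. Give the minimum detectable difference at the expected analysed number (about 0.9 SD at 39, unadjusted), with power over a range of smaller increments and any assumed baseline correlation stated.
5. State that a confidence interval that includes a worthwhile benefit will be reported as inconclusive, not as showing that coaching adds nothing.

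The cost is one rewritten paragraph. Stated power at f = 0.5 goes up, and the text becomes franker about smaller effects. No extra participants are needed.

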### Data analysis

Missing data, participant dropout and loss to follow-up will be minimised through careful trial management. Additionally, the rates of missing data on individual data collection forms will be monitored at each time point throughout the study.

The primary analyses will be undertaken on an intention-to-treat basis. Participant characteristics, participant engagement and intervention usage, and coaching acceptability will be described. A 2 (Group)× 3(Time) repeated measure ANOVA will be applied to compare continuous scores for primary and secondary outcomes between the intervention and comparison groups.

To explore possible attrition biases, we will also conduct analyses to compare retained participants and those lost after baseline assessment, using *t*-tests for continuous measures and chi-square-tests for categorical variables (eg, gender, family socioeconomic and clinical factors). Qualitative data collected using semi-structured interviews (eg, transcripts) will be examined by thematic analysis.

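### The 56 randomised do not absorb 30% attrition: about 39 parents would remain, not the 43 the plan requires

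*Protocol article*

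**What the plan says.** The Sample size section of the protocol article describes a G*Power calculation for F-tests (ANCOVA and ANOVA) on parental stress. It assumes an effect of f = 0.5, "with a power of 80% and α of 0.05 (two-tailed"), and concludes that "a sample size of 43 parents is required". It then adds an allowance for loss: "To allow an attrition of approximately 30% between baseline (T0) and follow-up assessment (T2), a sample size of 56 parents (28 per group") is needed. The abstract repeats the result: "A sample of 56 families will be randomised in a 1:1 ratio".

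No inflation formula is given, and no other attrition rate appears in the article. The numerator degrees of freedom, number of groups and number of covariates entered in G*Power are not stated either. The only outcome model described in the Data analysis section is a 2 (group) × 3 (time) design, in which a "repeated measure ANOVA will be applied to compare continuous scores for primary and secondary outcomes".

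**The concern.** An attrition allowance should ensure that the required number is still there after the expected loss. Here three linked figures are stated (43 required, about 30% lost, 56 randomised), and the third does not follow from the first two. If the trial loses exactly the share it predicts, it ends below its own target.

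At stake is the claim of 80% power on the basis that gave 43. So is the reader's view of how much dropout the trial can stand. The article itself names an insufficient sample as a risk (Strengths and limitations; Discussion), and a reader weighing that risk would take the tolerance to be about 30%.

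**Working it through.** **Inputs** (all from Sample size): required number n = 43; attrition d = 0.30 from T0 to T2; randomised N = 56 (28 per group); f = 0.5; α = 0.05; power 80%.

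**1. Reproduce the plan's figure.** Multiplying by (1 + d): 43 × 1.30 = 55.9, which rounds up to 56. This matches exactly. The article does not print this formula, so the multiplier is inferred.

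**2. The inflation that keeps 43.** n / (1 − d) = 43 / 0.70 = 61.4, so 62 (31 per group). That is 62 − 56 = 6 more than stated. Check: 62 × 0.70 = 43.4.

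**3. What 56 delivers.** 56 × 0.70 = 39.2, about 39 parents, or 28 × 0.70 = 19.6 per group. The shortfall is 43 − 39 = 4. This step does not depend on how 56 was obtained.

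**4. The attrition that 56 tolerates.** 1 − 43/56 = 0.232, or 23%.

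**5. Whether the word approximately closes the gap.**

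| Attrition | Needed to keep 43 | Left from 56 |
|---|---|---|
| 23% | 55.8 → 56 | 43.1 |
| 25% | 57.3 → 58 | 42.0 |
| 27% | 58.9 → 59 | 40.9 |
| 30% | 61.4 → 62 | 39.2 |

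It does not; the allowance already falls short at 25%.

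**6. Power.** This uses the noncentral F distribution with λ = f²N. Power is the probability that F(df1, df2, λ) exceeds its 5% critical value, with df2 = N − groups − covariates. As the G*Power settings are not stated, they are assumptions here:

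| Assumed setting, f = 0.5 | Smallest N for 80% | Power at 43 | Power at 39 |
|---|---|---|---|
| df1 = 2, six cells, one covariate | 43 | 0.810 | 0.764 |
| df1 = 2, three groups, no covariate | 42 | 0.814 | 0.769 |
| df1 = 1, two groups, one covariate | 34 | 0.892 | 0.860 |

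For the first row, λ = 0.25 × 43 = 10.75 with df2 = 43 − 6 − 1 = 36 at N = 43, and λ = 0.25 × 39 = 9.75 with df2 = 32 at N = 39. Of the rows shown, only the first returns exactly 43.

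**The case against.** The strongest reply accepts the arithmetic and disputes its consequence. It has three parts.

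- **The power loss rests on inferred settings.** Two numerator degrees of freedom, six cells and one covariate were chosen because they return 43, and nothing in the article confirms that they were used. This stands: the 76% is conditional. The gap between 39 and 43 is not.
- **A two-arm contrast may still be adequately powered.** With 1 numerator degree of freedom, f = 0.5 needs only 34 parents, and 39 give 86%. This also stands, so the point does not show that the main comparison is underpowered. But the plan states 43, not 34. If the 1-df comparison is the intended basis, then 43 itself needs correcting, and the sentence is wrong for a second reason.
- **The 30% runs to T2 (12 months), while the primary time point is T1 (6 months).** Loss by T1 may be smaller, and if it were 23% or less, 56 would keep 43 there. The article gives no T1 rate, however, and its own sentence ties 56 to loss by T2. The 2 × 3 model also uses T2; in its usual complete-case form it drops parents who miss that visit. How missing data will be handled is not stated in the article, so an analysed number of 39 is itself an inference.

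These points limit how much the error matters in practice. None makes the three stated figures consistent.

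**Conclusion.** The concern holds. On the plan's own figures, 56 randomised with 30% attrition leaves about 39 parents, 4 below the stated requirement, and the attrition that 56 tolerates is 23%. This needs no assumption beyond the article's numbers.

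The effect on power is less certain. It falls from 81% to 76% if the calculation used the settings that return 43, and is 86% at 39 for a 1-df two-arm comparison. All these values take f = 0.5 as given and assume that only completers are analysed. The sample-size statement must be corrected, but the error does not by itself show that the post-intervention comparison lacks power.

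**What to change.** Correct the attrition sentence in the Sample size section in one of these ways:

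1. **Restate the tolerance.** Keep 56 and say that it retains 43 completers for attrition of up to 23%.
2. **Restate the expected number and power.** Keep 56 and 30%, say that about 39 parents are then expected to remain, and give the power at 39 with the test and its degrees of freedom named (76% under the settings that return 43; 86% for a 1-df two-arm comparison).
3. **Raise the number.** If 43 completers must be assured at 30% loss, randomise 62 (31 per group) and change the abstract to match.

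Options 1 and 2 cost one sentence and a slightly less favourable figure, with no extra families. Option 3 costs 6 more families. Whichever is chosen, state the G*Power inputs behind 43 and whether the attrition rate refers to T1 or T2. The Recruitment section gives enrolment as January to December 2026 and T2 falls 12 months after randomisation, so the correction can be made before the results are known.

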### Outcomes and other measures

Outcome measures will be administered at baseline (T0), post-intervention (6 months post-randomisation, T1), and follow-up (12 months post-randomisation, T2).

The primary outcome of the study is parental stress. The self-report, seven-item Stress scale from the Depression Anxiety Stress Scales^42^-short form (DASS-21) will be used to assess nervous arousal, restlessness, impatience, irritability, overactivity and agitation. Each item is rated on a 4-point scale (0=never, 1=applied to me to some degree, or some of the time (sometimes), 2=applied to me to a considerable degree, or a good part of the time (often), or 3=applied to me very much, or most of the time (almost always)).

Secondary outcome measures include the following:

Parental depressive and anxiety symptoms, assessed by the Depression and Anxiety scales of the DASS-21,^42^ with higher scale scores indicating higher levels of depression and anxiety symptomatology, respectively.Family empowerment, using the 34-item Family Empowerment Scale (FES).^43^ Each item is rated by the parent on a scale ranging from 0=not applicable to 5=very often. An overall score can be computed to measure parents’ attitudes, knowledge and behaviours regarding empowerment in relation to their child. Higher scores indicate higher levels of empowerment.Family quality of life, measured by the 25-item Beach Center Family Quality of Life Scale (FQOL)^44^ to capture families’ perception of their quality of life across five domains: family quality of life: family interaction, parenting, emotional well-being, physical/material well-being and disability-related support. The scale uses a 5-point scale (1=very dissatisfied to 5=very satisfied), with higher scores indicating higher levels of family quality of life.Parental engagement in activities that promote their health, obtained through the 8-item Health Promoting Activities Scale^45^ (HPAS). Parent respondents estimate the frequency of their participation along a 7-point scale where 1=never to 7=once or more every day, and scores are totalled for an overall score. Higher scores indicate more frequent participation in activities that promote health.Child global health outcomes, using the Clinical Global Impression Scale.^46^ Originally developed for assessing patient outcomes in mental health conditions based on functional impact and clinical meaningfulness, the scale has been employed in studies in the context of various medical and neurodevelopmental conditions as a global rating of severity and change in interventional studies.^47 48^ In this trial, two of the three scale items will be used. Using a 7-point scale, the clinician will rate the child’s illness severity (CGI-S) and improvement or change (CGI-I) relative to their experience with other children with the same condition.

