### Study procedures

#### Enrolment and randomisation

Eligible parents of children assessed through the research-embedded Developmental Regression clinic will be provided with information about the intervention trial and invited to participate. For those who consent to this study, if data on the outcome measures were collected as part of their first assessment or a follow-up review at the clinic within the past 6 months (whichever is closer to their study enrolment), the data will be transferred and used as their baseline data (T0) in the trial. Specifically, direct identifiers (eg, names) will be replaced by a code before participant data are transferred to a research-only database using REDCap, a secure, web application to support data capture.^40^ A 1:1 randomisation allocation sequence will be computer-generated within REDCap to allocate parent participants to the FF group or Coaching+FF group, thereby ensuring that participants, coaches, trial coordinator, outcome assessors and the research team analysing the data are concealed from the group assignment until baseline assessment and allocation are completed. Outcome assessors (clinicians completing assessments of the child) will remain blinded to group allocation across the assessment timepoints.

Participants will also complete post-intervention (T1) and follow-up (T2) assessments via online questionnaires hosted in REDCap. Figure 2 outlines the participant flow.

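### CGI-Improvement is scheduled at pre-randomisation baseline with no stated within-child reference, so its T0 value is undefined or not comparable and T1/T2 ratings lack a common reference

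*Protocol article*

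**What the plan says.** Under Outcomes and other measures, the protocol article names the last secondary outcome as "Child global health outcomes, using the Clinical Global Impression Scale". Two clinician-rated 7-point items are used: severity (CGI-S) and improvement (CGI-I). The sentence describing them closes with the only reference offered for either item: "improvement or change (CGI-I) relative to their experience with other children with the same condition".

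The same section sets the visits for every outcome without exception: "Outcome measures will be administered at baseline (T0), post-intervention (6 months post-randomisation, T1), and follow-up (12 months post-randomisation, T2"). Table 2 agrees, marking CGI-I at T0, T1 and T2 in the same pattern as CGI-S. Study design places T0 before randomisation.

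Enrolment and randomisation allows T0 outcome data to be carried over from the clinic if they were collected "as part of their first assessment or a follow-up review at the clinic within the past 6 months", taking whichever is closer to enrolment.

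Data analysis names one between-arm method: "A 2 (Group)× 3(Time) repeated measure ANOVA will be applied to compare continuous scores for primary and secondary outcomes". It makes no exception for CGI-I and names no other test for it.

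**The concern.** A rating of improvement or change needs an earlier state of the same child to be compared with. The article schedules the rating at a visit where that state may not exist, and it names no such state for any visit. Comparison with other children can place a child on a severity scale, but it cannot say whether that child has changed.

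Two things are at stake. First, the T1 and T2 ratings, which carry the treatment comparison, could be made against different references by different raters or for different children. An analysis plan cannot repair this once the ratings are made. Second, if CGI-I goes into the three-visit ANOVA, the T0 column does not do the work of a baseline. For CGI-S, T0 is the pre-treatment level of the quantity measured again at T1 and T2. For CGI-I, the movement from T0 to T1 would be a change in a change rating, taken against references that are not stated.

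**Working it through.** The article gives no figure for CGI-I, so there is none to reproduce. The check has two parts.

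**1. The text set side by side**

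- *Schedule.* Table 2 and the opening of Outcomes and other measures both put CGI-I at T0. Because the two agree, a stray mark in the table is not a sufficient explanation.
- *Reference.* The sentence that defines the items gives one comparator, other children with the same condition. It does not mention the first visit, T0 or the previous visit.
- *What T0 is.* If T0 is the child's first assessment, the clinic has rated no earlier state. If T0 is a follow-up review (Study setting puts these at about 8 weeks, 6 months and 12 months), a clinician could rate change since the first visit, but the article does not say so. The T0 ratings of the two kinds of child would then not mean the same thing.
- *Analysis.* Child global health is a secondary outcome, and the 2×3 ANOVA is the only between-arm method stated for secondary outcomes.

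**2. What a T0 column does to the ANOVA (illustration)**

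Assumptions, none of them from the article except the arm size: 28 per arm (Sample size), no dropout, SD 1 at each visit, correlation 0.5 between T1 and T2, and a true difference d = 0.7 SD at both T1 and T2. The Group test compares each child's mean over the visits used.

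*T1 and T2 only.* Difference = 0.7. Variance of the child mean = (1 + 1 + 2×0.5)/4 = 0.75, SD 0.866. Standardised difference = 0.7/0.866 = 0.81.

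*T0 the same constant for every child (for example, no change).* Difference = (0 + 0.7 + 0.7)/3 = 0.467, which is two thirds of 0.7. Variance = (0 + 1 + 1 + 2×0.5)/9 = 0.333, SD 0.577. Standardised difference = 0.467/0.577 = 0.81. The numerator and the SD are both multiplied by 2/3, so the Group test is identical to the T1/T2 test.

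*T0 pure noise (SD 1, unrelated to T1 and T2).* Difference = 0.467. Variance = (1 + 1 + 1 + 2×0.5)/9 = 0.444, SD 0.667. Standardised difference = 0.467/0.667 = 0.70.

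Simulation under the same assumptions, 4,000 trials per setting:

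| T0 CGI-I | Power, Group | Power, Group × Time |
|---|---|---|
| Not used (T1/T2 only) | about 84–85% | – |
| Constant | 85% | 76% |
| Pure noise | 72% | 49% |

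With d = 0, rejection rates were 4.7% to 5.7% across all settings, so type I error stays near 5%. Both ANOVA terms are shown because the article does not say which one carries the comparison.

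**The case against.** The strongest reply is that the article is condensed. One closing phrase covers two items in a single sentence and may have been meant for CGI-S alone, with rater instructions held in the full protocol. That is possible. As written, however, the phrase covers CGI-I as well, and the T0 mark is positively stated in two places, so this is not merely detail left out.

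A second reply is that the ANOVA is said to apply to continuous scores, and a single 7-point item might fall outside that description. This stands in part: the link to the ANOVA is probable, not certain. If CGI-I is outside the ANOVA, the schedule and reference problems remain.

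A reader might infer more than the article supports in three ways:

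- *That no child can have a valid T0 rating.* This is too strong. Where T0 is a follow-up review, change since clinic entry can be rated. The fault is that the reference is unstated and not uniform.
- *That a constant T0 costs a third of the treatment effect.* The averaged raw difference is two thirds of the T1/T2 difference, but its SD shrinks equally and the Group test does not change.
- *That children whose T0 is a first assessment would be deleted from the analysis.* This needs T0 to be left blank and a complete-case rule. Table 2 schedules the rating, and the article states no such rule.

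**Conclusion.** The point holds. CGI-I is scheduled at a pre-randomisation visit where a change rating has no prior state for some children and an unstated, different one for others. Its T1 and T2 ratings have no stated common reference. These conclusions rest on the article's wording alone.

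The statistical consequence depends on the natural reading that CGI-I enters the 2×3 ANOVA, and on what raters record at T0. If the T0 ratings are arbitrary, power is lost: to 72% for Group, against about 84–85% for T1/T2 only, and to 49% for Group × Time, under the assumptions above. If T0 is constant, the Group test is unaffected, only the raw averaged difference is rescaled, and Group × Time has 76% power.

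The reach is limited to one of two items in one secondary outcome. Type I error, the primary outcome, the sample size and CGI-S are unaffected. The correction should be made because ratings already taken against an unclear reference cannot be recovered, but it does not threaten the trial's main conclusion.

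**What to change.** - Remove CGI-I from the T0 column of Table 2, and state the exception in the sentence that lists the outcome visits.
- Define CGI-I at T1 and T2 as change from that child's own T0 state. Keep the comparison with experience of other children for CGI-S only.
- State that arms are compared on CGI-I at T1 and T2 only, for example with an ordinal or rank-based method, optionally adjusted for T0 CGI-S. Keep the T0/T1/T2 analysis for CGI-S.

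The cost is a change to the schedule table, the rater instruction and the analysis wording, with one rating fewer at T0. Enrolment is planned from January to December 2026, and T1 falls 6 months after randomisation, so an early change to the rater instruction protects the most ratings. The change does not remove the variation in time since T0, which the Discussion already acknowledges as a limitation.
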